### Outcomes

#### Primary Outcomes

The primary outcomes of this registry study are to investigate practice variability and identify best practices, and to develop and validate clinical tools and AI models to optimize treatment planning, tumour targeting, assessment of treatment effect, and outcome prediction in patients undergoing TLA for primary or secondary liver tumours.

#### Secondary Outcomes

Secondary outcomes include safety and efficacy of TLA. Safety will be assessed by monitoring complications, up to 3 months following TLA, according to the CIRSE classification system for complications [17]. Perioperative complications are defined as those occurring up to 1 month following TLA, while delayed complications are those occurring after 1 month. Efficacy will be assessed as disease status at different time points, time-to-progression, disease-free survival (DFS), local tumour progression free survival, and OS according to standard terminology [19, 20]. Other outcomes that will be assessed are resource consumption and total costs associated with the clinical pathway of TLA will be assessed from the hospital's perspective. A micro-costing approach utilizing the time-driven activity-based costing will be conducted [18].

### Sample Size

The sample size was not predetermined, as this is a registry study. However, approximately 1200 patients are expected to be required for development of aforementioned AI algorithms. Prospective inclusions began on January 17th 2024. This project is designed to continuously include new patients providing an ongoing source for studies aimed at optimizing clinical outcomes of TLA.

### Statistical Analysis

Descriptive findings will be summarized with means and standard deviations (SD). Continuous variables will be presented with means and SD or ranges for nonparametric distributions. Categorical variables will be shown as numbers and percentages. Kaplan–Meier estimates will be used to assess local and overall recurrence, DFS, and OS. Logistic and Cox regression analyses will be performed to determine predictors for local and overall recurrence, DFS, and OS. The methods used for feature selection and model generation will be based on the extent of data availability. Data will be analysed using R (version 4.2.1; R Core Team, 2023, Austria). Cost of clinical pathway of TLA will be analysed using IBM SPSS Statistics (version 29, IBM, Armonk, USA).

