Alongside the more prominent application of TLA, a wide variety of advanced software tools has become available to improve treatment planning, tumour targeting, and assessment of immediate and long-term treatment response. In recent years, artificial intelligence (AI) models for planning and evaluation have gained interest, as they can aid in improving workflows in different clinical settings. Although these technical advancements were expected to deliver consistent outcomes with minimal operator dependency, they are still not widely used and have paradoxically led to greater diversity in workflow practices [12, 13]. The consequence of this treatment and workflow variability imposes the risk of being followed by inconsistency in clinical outcomes among treating physicians and centres. This variability hampers implementation of TLA as standard of care. For this reason, the European Union funded, A-IMAGIO (Ablation-IMaging and Advanced Guidance for workflow optimization in Interventional Oncology) project was initiated. One of the main goals of the A-IMAGIO project is to expedite the adoption and acceptance of multimodality ablation therapy as treatment of first choice for primary and secondary liver tumours by optimizing treatment workflow and reducing treatment variability.

Within the A-IMAGIO study, data are collected from various centres to gain insight into inter-centre treatment variability and outcomes. This knowledge will be used to identify best practices and techniques and eventually develop a standardized and optimal workflow for TLA.

To support and improve this, clinical and imaging data will be used to develop and validate machine learning and deep learning (DL) based models that allow software-based treatment planning, needle guidance, and assessment of treatment effect.

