## Materials and Methods

### Trial Design and Study Setting

This prospective, international, multicentre registry study is coordinated by Leiden University Medical Centre (The Netherlands) and Maastricht University Medical Centre + (The Netherlands). Participating centres include Radboud University Medical Center (The Netherlands), Amsterdam University Medical Centre (The Netherlands), Istituto Nazionale dei Tumori di Milano (Italy), University Hospital of Innsbruck (Austria), Lausanne University Hospital (Switzerland), University Medical Centre Utrecht (The Netherlands), Henri Mondor University Hospital (France), and Newcastle Freeman Hospital (UK). Other centres will be welcome and/or invited to participate.

A detailed overview of the collected data concerning patient and tumour characteristics, ablation technique, and treatment outcomes is described in supplementary 1. Additionally, imaging data will be collected on treatment planning, assessment, and follow-up. To expand the database, retrospective data and data obtained from previously conducted or ongoing prospective studies on TLA of primary and secondary liver tumours will be used [14–16].

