### Intervention

To provide the opportunity to assess current practice, and techniques, identify areas of heterogeneity and identify best practices, patients will undergo percutaneous TLA as standard of care of the participating centre. The procedure is allowed to be performed under general anaesthesia or deep sedation, and the choice of ablation method (MWA or RFA), apparatus, ablation settings, and image guidance techniques for needle placement is also left to the discretion of the treating physician. All patients will undergo a dual-phase contrast-enhanced (cone-beam) CT scan with at least an arterial and portovenous phase immediately before and after the procedure. Contrast can be administered either intravenously, or through a catheter in the hepatic artery, also known as CT hepatic arteriography. Assessment of technical success (i.e. complete eradication of the tumour with sufficient ablation margin) can be evaluated by visual assessment, image co-registration software, and/or confirmation software. As standard of care, a circumferential minimal ablation margin (MAM) of at least 5 mm is generally aimed for.

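### The stated summary for non-normal continuous variables, a mean with a range or a range alone, is unsuitable, and if tabulated by centre it would mix apparent spread with centre size

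*Protocol article*

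**What the plan says.** All references are to the protocol article.

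- **Statistical Analysis, general rule.** The section opens with "Descriptive findings will be summarized with means and standard deviations (SD", with no exception for distributional shape.
- **Statistical Analysis, continuous variables.** The next sentence reads "Continuous variables will be presented with means and SD or ranges for nonparametric distributions".
- **Statistical Analysis, categorical variables.** "Categorical variables will be shown as numbers and percentages".
- **Primary Outcomes.** "The primary outcomes of this registry study are to investigate practice variability and identify best practices". The Introduction places this at centre level: "data are collected from various centres to gain insight into inter-centre treatment variability and outcomes".
- **Intervention.** Practice is not standardised but set by the physician: "the choice of ablation method (MWA or RFA), apparatus, ablation settings, and image guidance techniques for needle placement is also left to the discretion". Most of these choices are categorical, but ablation settings are plausibly continuous, and the minimal ablation margin is measured in millimetres.
- **Sample Size and Study Setting.** "approximately 1200 patients are expected to be required for development of aforementioned AI algorithms". Ten centres are named (two coordinating, eight participating), and "Other centres will be welcome and/or invited to participate". Recruitment per centre is not given.

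**The concern.** The article does not leave this question open. It states a rule for non-normal variables, and the rule is a poor one. On the literal reading the reader gets a mean, which a few extreme patients can shift, and a range, which two patients determine. On the other reading there is a range and no measure of location at all. Neither gives the typical value and the middle spread that a skewed variable calls for. The rule also fits badly with the sentence before it, which assigns mean and SD to everything.

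This weakness applies even to the pooled cohort. It matters somewhat more here because practice variability is a primary outcome and the section names no other summary for continuous practice variables: its survival and regression methods are directed at recurrence, disease-free survival and overall survival. The range has a particular drawback for comparing centres, because its expected width depends on the number of patients as well as on how variable they are. Two centres with the same practice but different volumes would tend to show different ranges.

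**Working it through.** The article gives no figure to reproduce here, so the check is of how the named statistics behave.

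**1. Inputs from the article.** About 1200 patients and ten named centres, hence 1200/10 = 120 per centre on average. Nothing is said about how unequal the centres are.

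**2. Assumptions, not in the article.** Centre sizes of 30, 120 and 300. Every centre is drawn from the same distribution, so true variability is identical. Skewed variables are log-normal with median 1 and log-SD s = 0.5, 0.8 or 1.0. A normal variable serves as a benchmark only, since the plan would give it an SD.

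**3. Range.** For n independent patients with distribution function F, the expected range is

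E(Rₙ) = ∫ [1 − F(x)ⁿ − (1 − F(x))ⁿ] dx,

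which rises with n for any fixed F that is not degenerate. Simulation with 10,000 replicates per setting gave the values below; numerical evaluation of the integral agrees to within about 1%.

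| Distribution | n = 30 | n = 120 | n = 300 | 120 / 30 | 300 / 30 |
|---|---|---|---|---|---|
| Normal (SD units) | 4.09 | 5.14 | 5.75 | 1.26 | 1.41 |
| Log-normal, s = 0.5 | 2.49 | 3.42 | 4.06 | 1.37 | 1.63 |
| Log-normal, s = 0.8 | 5.34 | 8.19 | 10.48 | 1.53 | 1.96 |
| Log-normal, s = 1.0 | 8.72 | 14.29 | 19.10 | 1.64 | 2.19 |

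For example, 4.06/2.49 = 1.63 and 19.10/8.72 = 2.19. From 30 to 300 patients the expected range therefore grows by 41% in the normal case and by 63% to 119% in the skewed cases.

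**4. How often the larger centre looks wider.** In the skewed cases the centre of 300 had the wider range in 91% to 92% of simulated pairs. This is close to what one expects when the range is governed mainly by the single largest value: with 330 patients from one distribution, the largest falls in the bigger centre with probability 300/330 = 0.91.

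**5. Alternatives on the same simulated data.**

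| Statistic | s | n = 30 | n = 300 | Ratio |
|---|---|---|---|---|
| Interquartile range | 0.5 | 0.657 | 0.684 | 1.04 |
| | 0.8 | 1.094 | 1.129 | 1.03 |
| | 1.0 | 1.419 | 1.449 | 1.02 |
| SD | 0.5 | 0.585 | 0.602 | 1.03 |
| | 0.8 | 1.212 | 1.293 | 1.07 |
| | 1.0 | 1.922 | 2.099 | 1.09 |

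The larger centre had the wider interquartile range in about 58% of pairs, not far from an even split. The strong size dependence belongs to the range, the statistic that the plan reserves for non-normal variables.

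**6. Location.** For a log-normal variable with median 1 the mean is exp(s²/2): exp(0.125) = 1.13, exp(0.32) = 1.38 and exp(0.5) = 1.65. Under these assumptions the mean lies 13% to 65% above the value of the typical patient.

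**The case against.** A reader might infer that the registry's primary description will show larger centres as more variable. The article does not support that. It would require ranges to be tabulated by centre, skewed continuous variables to be the practice measures, and range width to be read as the measure of variability. The article states none of these. The Statistical Analysis paragraph is generic and mentions neither centres nor practice variability.

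Three further points stand:

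- Most practice choices listed under Intervention (anaesthesia or sedation, ablation method, apparatus, image guidance, contrast route, method of margin assessment) are categorical. They will be shown as counts and percentages, so the range rule does not touch them.
- Variability between centres is not the same as spread among patients within a centre. Differences between centres appear chiefly in proportions and typical values, which a size-dependent range does not by itself misstate.
- Centre sizes and skewness are assumptions. The percentages describe the range as a statistic and are not estimated effects on this registry.

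It can also be said that the sentence is loosely worded, that the authors may have meant medians with interquartile ranges, and that a condensed article leaves table formatting to a fuller document. This carries less weight. The article did choose to state a rule, and the rule as written names neither a median nor an interquartile range. If something else was meant, the sentence still needs correcting.

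**Conclusion.** The point holds in a limited form and is minor. The Statistical Analysis section fixes an unsuitable summary for non-normal continuous variables, and its first two sentences overlap without agreeing. That much follows from the text on either reading of the second sentence, and it applies to the pooled cohort as well as to any table by centre.

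The consequence for the primary outcome is conditional. If the summaries are reported by centre for continuous practice variables such as ablation settings or ablation margin, and their ranges are compared, apparent spread would be confounded with centre size. Under the assumed sizes of 30 and 300, with equal true spread, the range would differ by about 41% (normal) to roughly 60% to 120% (log-normal, log-SD 0.5 to 1.0), against about 2% to 5% for the interquartile range. For 30 against the ten-centre average of 120, the skewed cases give 37% to 64%. No test, model, survival estimate or sample size depends on the sentence.

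**What to change.** Replace the first two sentences of the Statistical Analysis paragraph with:

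> Continuous variables are presented as mean and SD if approximately symmetric, otherwise as median and interquartile range, overall and by centre; minimum and maximum may be added but are not used to compare variability between centres.

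This removes the overlap between the two sentences and settles what is shown for skewed variables. It costs one sentence. It needs no additional data, and the sentence on categorical variables and the planned survival and regression analyses stay as they are.

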**Materials and Methods:**

This is a prospective, international, multicentre, observational registry study. Patients will be included with age ≥ 18 years, diagnosed with primary or secondary liver tumours, and undergoing thermal liver ablation. A detailed dataset of medical history, baseline clinical and imaging parameters, tumour characteristics, ablation technique/parameters, treatment outcomes, periprocedural images, and adverse events, will be collected for all participants. This data will be used to develop AI algorithms for prognostic modelling and quantitative imaging analysis. Additionally, costs associated with thermal liver ablation clinical pathway will be evaluated.

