### Follow-Up

Follow-up will be conducted according to the standard of care of the participating centre. In general, the follow-up of TLA encompasses physical blood tests and imaging such as (CE)CT, MRI, and/or PET-CT, scheduled at three to 6 months intervals. Patients will be monitored for 5 years following inclusion in the study. Follow-up scans will be reviewed by an experienced radiologist, as per standard of care.

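### Kaplan–Meier for local and overall recurrence, read naturally, censors deaths and so overstates the absolute recurrence risk; by how much depends on mortality that the protocol does not give

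*Protocol article*

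**What the plan says.** The Statistical Analysis section of the protocol article fixes the estimator: "Kaplan–Meier estimates will be used to assess local and overall recurrence, DFS, and OS". The next sentence covers regression: "Logistic and Cox regression analyses will be performed to determine predictors for local and overall recurrence, DFS, and OS".

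The Secondary Outcomes section lists the efficacy measures as disease status at several times and "time-to-progression, disease-free survival (DFS), local tumour progression free survival, and OS according to standard terminology". It does not say how a death enters each of them; that is left to cited sources. The Follow-Up section gives the horizon: "Patients will be monitored for 5 years following inclusion in the study". The abstract describes the population: "Patients will be included with age ≥ 18 years, diagnosed with primary or secondary liver tumours, and undergoing thermal liver ablation".

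The article names no cumulative incidence function or other competing-risk method, and gives no rule for deaths before recurrence. It states no recurrence rate and no mortality rate. An article may leave such detail to a fuller plan, but here the estimator for recurrence is stated outright.

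**The concern.** Kaplan–Meier suits DFS and OS because death is an event in both. Recurrence is different. A patient who dies without recurrence can no longer recur, yet Kaplan–Meier treats that patient as censored and still able to recur later. The complement of the curve then answers a hypothetical question: how many would recur if nobody died first. The share of patients who do recur is smaller whenever some die first.

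Patients with primary or secondary liver malignancy who are followed for 5 years can be expected to include such deaths. For local recurrence, the competing deaths include those after distant progression as well as those free of all disease.

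At stake is the absolute recurrence risk that the registry reports. The article names discrepancies in reported oncological outcomes as an obstacle to wider use of ablation, and it intends a prognostic model for early recurrence to inform individual treatment. Both uses call for the risk that patients actually face.

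**Working it through.** **Does the text imply that deaths are censored?** Overall recurrence and DFS stand as separate items in the same sentence. If death counted as an event in overall recurrence, that item would essentially duplicate DFS, so censoring at death is the natural reading. Time-to-progression, by its name, is also not a composite with death. For local recurrence the inference is weaker, because the term may be shorthand for local tumour progression free survival, whose definition is not given.

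**Inputs.** From the article: the 5-year horizon. Assumed, because the article gives no figure:
- the 5-year 1−KM for recurrence, R (20% for local, 50% for overall)
- the net 5-year mortality without the recurrence in question, D (5% to 50%)
- constant, independent cause-specific hazards

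The article states no recurrence figure, so there is none to reproduce.

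**Formulas.**
- Recurrence hazard: a = −ln(1 − R)/5
- Hazard of competing death: b = −ln(1 − D)/5
- With deaths censored: 1−KM at 5 years = 1 − exp(−5a) = R
- Cumulative incidence at 5 years: CIF = a/(a + b) × [1 − exp(−5(a + b))]

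**One case in full, R = 20%, D = 40%.**
- 5a = −ln(0.8) = 0.2231 and 5b = −ln(0.6) = 0.5108
- a/(a + b) = 0.2231/0.7340 = 0.3040
- 1 − exp(−0.7340) = 1 − 0.8 × 0.6 = 0.52
- CIF = 0.3040 × 0.52 = 0.158

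So 1−KM reads 20% where 15.8% of patients recur, a ratio of 20/15.8 or about 1.27.

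**Across the assumed range.**

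| Net competing mortality | CIF when 1−KM is 20% | Relative overstatement | CIF when 1−KM is 50% |
|---|---|---|---|
| 5% | 19.5% | about 2% | 48.9% |
| 10% | 19.0% | about 5% | 47.7% |
| 20% | 18.0% | about 11% | 45.4% |
| 30% | 16.9% | about 18% | 42.9% |
| 40% | 15.8% | about 27% | 40.3% |
| 50% | 14.6% | about 37% | 37.5% |

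The two CIF columns should not be read at the same row for one population. Death after a distant recurrence competes with local recurrence but not with overall recurrence, so the competing mortality for overall recurrence should be the lower of the two.

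**Check by simulation** (1,200 patients, 400 replicates, D = 30%). With R = 20%, 1−KM averaged 20.0% and the observed proportion recurring 16.9%. With R = 50%, the averages were 50.0% and 42.9%. Both agree with the formulas.

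**What this does to a comparison of centres.** The expression for 1−KM contains a but not b. Two centres with the same recurrence hazard at R = 20% therefore both read 20%, whether mortality is 5% or 50%. The cumulative incidence is what moves, from 19.5% to 14.6%.

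**The case against.** Five arguments can be made on the other side.

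- **Deaths may not be censored.** The endpoint definitions lie in cited sources that are not shown, and local recurrence may mean local tumour progression free survival. If that composite counts death as an event, Kaplan–Meier is valid for it. This stands as a possibility for local recurrence. It does not help overall recurrence, which would then repeat DFS.
- **The mortality is unknown.** The introduction discusses early-stage hepatocellular carcinoma and small oligometastatic disease, while the eligibility table sets no stage limit. Competing mortality could be low. This stands: at 5% the error is trivial.
- **Centre comparisons are not shown to be distorted.** A reader might infer that centres with sicker patients would appear to have worse local control. Under the assumptions used above they would not, since 1−KM does not depend on mortality. Cumulative incidence would instead make a centre with higher mortality look better on recurrence. Dependent censoring, for example through liver function or tumour biology, could distort the ranking. It is plausible, but nothing in the document shows its size or direction.
- **The regression is already sound.** Cox models for recurrence with deaths censored are cause-specific hazard models. This stands, and it confines the fault to absolute risk.
- **Little rests on the curve.** Efficacy is a secondary outcome, and no stated test or decision rule uses these estimates. The prognostic model concerns early recurrence, a shorter horizon over which fewer competing deaths accrue, so the 5-year gaps do not carry over to it. This lowers the weight of the point but does not remove it.

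**Conclusion.** The concern holds for absolute recurrence risk. Kaplan–Meier is stated for local and overall recurrence, the natural reading censors deaths, and 1−KM then exceeds the probability of recurrence that patients experience whenever some die first. The direction follows from that reading; the size is assumed. With 1−KM of 20% and constant independent hazards, the excess runs from 0.5 percentage points at 5% competing mortality (20.0 − 19.5) to 5.4 points at 50% (20.0 − 14.6), and it becomes material from about 20–30%.

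Stronger readings are not supported. The document gives no basis for calling the competing mortality high, a false ranking of centres is not demonstrated, and the planned Cox models are not at fault. Severity is moderate: the estimator should be corrected, but the design and the other analyses do not depend on it.

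**What to change.** In the Statistical Analysis section:

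- Keep Kaplan–Meier for DFS, OS and any composite that counts death as an event, such as local tumour progression free survival if it is so defined.
- Estimate local recurrence, overall recurrence and time-to-progression by Aalen–Johansen cumulative incidence, with death without the event in question as the competing event.
- State for each endpoint how death enters it, and say whether local recurrence and local tumour progression free survival are the same quantity.
- Interpret the planned Cox models for recurrence as cause-specific, and use these, not the cumulative incidence curves, to compare practices.
- Where the early-recurrence model reports an absolute risk, allow for competing death.

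The cost is a change of wording. Deaths are already needed for OS, so no new data are collected. The downside is that two types of curve must be presented and explained.

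### Logistic regression is named beside Cox for recurrence, DFS and OS with no fixed time point, although follow-up in this registry will be unequal

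*Protocol article*

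**What the plan says.** The Statistical Analysis section names two regression models for the same four outcomes: "Logistic and Cox regression analyses will be performed to determine predictors for local and overall recurrence, DFS, and OS". It gives no time point for the logistic models, does not divide the outcomes between the models, and does not say which result counts if they disagree. The sentence before it reads "Kaplan–Meier estimates will be used to assess local and overall recurrence, DFS, and OS", so the plan itself treats these outcomes as censored.

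Three other sections determine how follow-up will be distributed:

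- **Sample Size:** "Prospective inclusions began on January 17th 2024", and "This project is designed to continuously include new patients providing an ongoing source for studies aimed at optimizing clinical outcomes of TLA".
- **Follow-Up:** "Patients will be monitored for 5 years following inclusion in the study", with imaging generally "scheduled at three to 6 months intervals".
- **Trial Design and Study Setting:** older data are to be pooled in: "To expand the database, retrospective data and data obtained from previously conducted or ongoing prospective studies on TLA of primary and secondary liver tumours will" […]. Further centres may also join.

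Two more places bear on the choice of model. Secondary Outcomes states: "Efficacy will be assessed as disease status at different time points, time-to-progression, disease-free survival (DFS), local tumour progression free survival, and OS". The section on the early-recurrence model uses Cox regression, not logistic, to identify clinical factors.

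**The concern.** Logistic regression needs a binary outcome. For DFS, OS and recurrence, such an outcome is well defined only at a stated time, with a rule for patients not observed that long. Without one, the default is to model whether an event has been recorded by the data cut. A patient followed for three months and a patient followed for five years then enter on the same footing.

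This matters here because one primary aim is to describe practice variability and identify best practices. The Introduction and the closing section describe planning, guidance and evaluation tools that have been changing over time. If a tool or centre is represented mainly by recent patients, its patients have had less time to show an event. A model that ignores follow-up time would credit the tool or centre with that difference.

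**Working it through.** The article states no figure to reproduce. The figure of about 1200 patients is an expectation given without inputs. The check therefore asks how large the artefact could be when there is no true difference.

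**Inputs**
- From the article: open-ended enrolment since 17 January 2024, 5 years of monitoring per patient, pooled older data, about 1200 patients.
- Assumed, because the article does not give them: a constant event hazard *h*, equal in both groups, and uniform follow-up on the windows shown.

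**Step 1. Closed form.** With follow-up uniform on (0, T), the proportion with an event seen is

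p(T) = 1 − (1 − e^(−hT)) / (hT).

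At h = 0.15 per year:
- T = 3: 1 − (1 − e^(−0.45))/0.45 = 0.195, odds 0.242
- T = 2: 1 − (1 − e^(−0.30))/0.30 = 0.136, odds 0.157
- T = 1: 1 − (1 − e^(−0.15))/0.15 = 0.071, odds 0.077

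| Newer vs older follow-up | Events seen | Odds ratio (true hazard ratio 1.0) |
|---|---|---|
| 0–1 vs 0–3 years | 7.1% vs 19.5% | 0.077/0.242 = 0.32 |
| 0–2 vs 0–3 years | 13.6% vs 19.5% | 0.157/0.242 = 0.65 |
| equal windows | equal | 1.0 |

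For 0–1 versus 0–3 years the odds ratio is 0.33 at h = 0.05 and 0.31 at h = 0.25. The assumed hazard hardly matters; the assumed gap in follow-up decides the result.

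**Step 2. A wider gap, up to the planned 5 years.** For follow-up uniform on (a, b), p = 1 − (e^(−ha) − e^(−hb)) / (h(b − a)), with h = −ln(1 − annual risk). Older patients have 2.5–5 years and newer patients 0–2.5 years.

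| Annual risk | Events seen, older vs newer | Odds ratio |
|---|---|---|
| 5% | 17% vs 6% | 0.31 |
| 10% | 32% vs 12% | 0.29 |
| 20% | 56% vs 23% | 0.24 |
| 30% | 73% vs 34% | 0.19 |

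**Step 3. Simulation of the alternatives.** 1200 patients split equally, 300 replicates, no true difference, the same windows as Step 2, annual risks of 5%, 10% and 20%.

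| Analysis | Mean estimate | Null rejected at 5% level |
|---|---|---|
| Logistic, event ever observed | OR 0.31 / 0.28 / 0.24 | 100% / 100% / 100% |
| Cox | HR 1.00 / 1.00 / 1.00 | 4% / 6% / 5% |
| Logistic at 1 year, only patients with at least 1 year of potential follow-up | OR 1.00 / 1.00 / 0.99 | 6% / 6% / 5% |

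With follow-up of 0–5 years in both groups, logistic regression on event ever observed gave odds ratios between 0.985 and 1.012 and rejected in 5–6% of replicates. The artefact therefore needs a link between the factor and length of follow-up.

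The restricted 1-year analysis loses patients. In the newer group (2.5 − 1)/2.5 = 60% qualify, 360 of 600, so on average 960 of 1200 are analysed.

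**The case against.** The strongest objection is that the article never defines the logistic outcome. A reader might infer that patients with short follow-up are counted as event-free and that newer techniques will therefore look better. The document supports neither step. It has no such coding rule, and it gives no adoption dates, no data-cut date and no follow-up lengths for the pooled older data. The direction and size of any bias are therefore assumptions.

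A valid use of logistic regression is also visible. Disease status at set time points is listed among the efficacy measures, and Step 3 shows that a fixed-time logistic analysis can be unbiased. Kaplan–Meier and Cox are already planned for the same outcomes, and nothing makes the logistic results the basis for naming best practices. Finally, a condensed article may leave horizons and censoring rules to a fuller document.

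Most of this stands, and it limits the point to a conditional one. It does not remove it. The sentence does not assign logistic regression to disease status at time points. It assigns it to recurrence, DFS and OS, next to Cox and without precedence. That is a stated model choice that takes no account of censoring, not just a missing detail, and a later document could repair it only by narrowing the sentence. Naming Cox as well does not settle which set of predictors would be reported if the two differ.

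**Conclusion.** The point holds in conditional form. The article assigns logistic regression to four censored outcomes, with no time point and no order between the two models, in a registry whose follow-up will be unequal. If the outcome is event ever observed and a factor is tied to enrolment date, the spurious association can be large. The odds ratio is about 0.32 for 0–1 versus 0–3 years and 0.65 for 0–2 versus 0–3 years at an assumed hazard of 0.15 per year, and 1.0 when follow-up is equally distributed. These figures rest on assumed constant hazards and uniform follow-up windows.

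The sentence should be fixed, but this is not a fatal defect, since censoring-aware methods are already in the plan for the same outcomes.

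**What to change.** Reword the regression sentence in Statistical Analysis along these lines:

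*Predictors of recurrence (local and overall), DFS and OS will be assessed with Cox models, cause-specific for recurrence. Logistic regression will be used only for binary outcomes at a stated time point, such as disease status at that point, either among patients whose potential follow-up reaches it or with censoring handled by inverse-probability-of-censoring weights or pseudo-observations.*

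Restriction by potential follow-up deals only with censoring at the data cut. Patients lost earlier still need weights or pseudo-observations.

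The cost is one sentence and slightly more analysis work, or fewer patients in the fixed-time analyses if restriction is chosen. No additional data are needed. The change also brings the section into line with the early-recurrence model, which already uses Cox for clinical factors.
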